### Primary outcome

Plasma levels of IL-6 and TNF-α will be determined using the ELISA (*enzyme-linked immuno sorbent assay*) method with high sensitivity kits (Quantikine^®^HS, R&D Systems Minneapolis, USA). Samples will be read with an adjusted microplate reader for 490 nm and wavelength correction to 650 nm. TNF-α acts at two known receptors: TNFR1 and TNFR2. In humans, the measure of circulating levels of the two soluble receptors is useful in determining the global production of TNF-α in plasma [32].

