### Sample size

The sample size was calculated after a previous pilot study with 12 participants, considering a confidence interval of 95%, a bilateral hypothesis test, a significance level of 0.05 (type I error), a power of 80% (type II error) and a crossover design for a statistical analysis of ANOVA. First, we calculated the size effect (f) for the partial ANOVA for the 12 participants, according to Portner & Watkins [39]. We use the functional performance (time in seconds of the TUG). We considered two freedom degrees and a power of 80%. It was determined that, considering a moderate effect size (0.5) for a minimum clinically significant difference, 13 volunteers will be needed in each group.

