### Statistical analysis

The statistical analysis will be conducted using SPSS 15.0 in Windows. In order to verify data normality, the Shapiro-Wilk test will be used. A comparison of the variables of muscle strength, functional capacity and plasma levels of IL-6 and TNF-α, before and after the intervention and three months after the completed intervention, will be conducted using ANOVA. A post hoc analysis will be conducted to find possible differences. A correlation among the variables will be analyzed using the test of Pearson's correlation. An association among the variables of IL-6 and TNF-α plasma levels, functional capacity and muscle strength will be analyzed using a linear regression. The significance level will be p = 0.05.

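### IL-6 and TNF-α are both primary and each is tested at 0.05 with no joint rule: if either one counts as success, the false-claim rate is about 7% to 10%

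*Protocol article*

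**What the plan says.** The Primary outcome section of the protocol article has a singular heading but covers two variables: "Plasma levels of IL-6 and TNF-α will be determined using the ELISA". Neither is marked as the leading one.

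The Statistical analysis section compares strength, functional capacity and the two markers "before and after the intervention and three months after the completed intervention, will be conducted using ANOVA". It then adds "A post hoc analysis will be conducted to find possible differences", without naming a method, and closes with "The significance level will be p = 0.05".

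The Background section states the hypothesis as an expected reduction in both cytokines. Question 1 in Methods/Design asks only whether changes will occur in the listed variables. Neither place says what pattern of results on the two markers would count as a positive trial.

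**The concern.** A single level of 0.05 gives a 5% chance of a false primary claim only if there is one primary test, or if success requires every primary test to be significant. Here there are two primary variables and two separate comparisons. With no stated rule, the text lets an author present a significant IL-6 result alone, or a significant TNF-α result alone, as the primary finding at a nominal 5%.

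The Conclusions section expects the results to have implications for new treatment strategies, so the primary comparison is more than exploratory. With 13 women per group and a sample size derived from a different variable (TUG time), one significant marker out of two is a plausible outcome, and one that is easily over-read.

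**Working it through.** **Inputs**

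- Number of primary variables: 2 (Primary outcome section).
- Level per test: 0.05, with no split or order (Statistical analysis section). The test is taken as two-sided, as in the Sample size section.
- Correlation between the two test statistics: not given. Assumed range 0 to 0.9. The Background says that TNF-α sets off a cascade that includes IL-6, which suggests some positive dependence. It also describes a separate release route for exercise-induced IL-6, so a high correlation cannot be taken for granted.
- Success rule: not given. Both readings are worked out below.
- One decisive test per marker. Post hoc contrasts are not counted.

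**Reading A: either marker counts.** With no true effect on either marker,

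P(at least one false claim) = 1 − P(|Z₁| < 1.96 and |Z₂| < 1.96).

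Under independence this is 1 − 0.95² = 0.0975. The upper bound under any dependence is 0.05 + 0.05 = 0.10. For correlated statistics, a bivariate normal calculation gives:

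| Correlation | Chance of at least one false primary claim | Multiple of 0.05 |
|---|---|---|
| 0 | 0.0975 | 1.95 |
| 0.5 | 0.0907 | 1.81 |
| 0.7 | 0.0835 | 1.67 |
| 0.9 | 0.0704 | 1.41 |

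The independence figure is exact for any two tests of level 0.05. The other rows treat the tests as two-sided normal tests and so approximate the ANOVA.

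**Reading B: both markers required.** A false claim then needs a false rejection on at least one truly null marker, tested at 0.05, together with significance on the other. The error is at most 0.05.

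**Cost of controlling the error, on the article's own planning inputs.** The Sample size section gives "a bilateral hypothesis test, a significance level of 0.05 (type I error), a power of 80% (type II error", then "We considered two freedom degrees and a power of 80" per cent, and concludes "considering a moderate effect size (0.5) for a minimum clinically significant difference, 13 volunteers will be needed in each group". First, the stated figure: reading 0.5 as Cohen's f in a one-way ANOVA with 2 numerator degrees of freedom (three cells of n), the noncentrality is f² × 3n. The smallest n reaching 80% power is 14, within one of the stated 13. At n = 13 the noncentrality is 0.25 × 39 = 9.75 on (2, 36) degrees of freedom, and power is 0.769.

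The same calculation at 0.025, the first Holm step, gives power 0.666 at 13 per group and needs 17 per group for 80%.

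**Check of the remedy.** Two independent tests at 0.025 give 1 − 0.975² = 0.0494, and the bound under any dependence is 0.05. Under a fixed order, the first marker keeps 0.05 and its power of 0.769. The second can be claimed only if the first is significant: with independent tests and the same true effect on both, that is 0.769 × 0.769 = 0.59.

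**The case against.** The strongest reply is that this is a condensed article. Multiplicity rules are commonly left to an analysis plan, which may exist and is not shown, and a level of 0.05 is compatible with Holm's procedure at an overall 0.05. That limits how far the point can go, but does not remove it. The point rests on what is printed: two primary variables, an ANOVA for each, and one level. Followed as written, that rule lets either marker support a claim.

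A second reply is that the hypothesis joins the two cytokines, so both must fall. That wording expresses an expectation and sets no decision rule, and Question 1 asks only about changes. It does show that the both-required reading is open, so the inflation must be stated as conditional.

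Three stronger readings are tempting, and the article does not support them:

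- A reader might infer that the error is nearly doubled outright. That needs the either-marker rule and low to moderate correlation; at 0.9 the factor is about 1.4.
- A reader might take "a significance level of 0.05 (type I error") in the Sample size section as a broken promise about the primary outcome. That 0.05 belongs to a calculation on TUG time, a secondary outcome, and makes no claim about the markers.
- A reader might count all ten variables and reach 1 − 0.95¹⁰ = 0.40. Eight of them are already labelled secondary, and six come from one dynamometer test, so independence is implausible and the figure says little about a false primary claim.

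**Conclusion.** The point holds in conditional form. If either marker suffices, the chance of a false primary claim is about 7% to 10% over correlations from 0.9 down to 0. If both are required it is at most 5%, but the article does not set that requirement. The range rests on an assumed correlation and on one test per marker. It should be corrected before the results are analysed, but it does not undermine the design.

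**What to change.** Add to the Statistical analysis section that the primary comparisons for the two markers are controlled at an overall two-sided 0.05 by one named method:

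- Holm's procedure: the smaller p-value is tested at 0.025 and, if significant, the other at 0.05; or
- a fixed order set in advance: the first marker is tested at 0.05, and the second, also at 0.05, only if the first is significant.

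Add that the outcomes listed under Secondary outcomes support no confirmatory claim. Leave the planned ANOVA over the three time points as it is; changing the comparison is a separate decision. The Questions/Hypotheses list names sTNFr where the Primary outcome section names TNF-α, so the added text must use whichever variable is settled as the second primary.

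The cost is a sentence or two and some power. Under Holm, a marker that has to pass at 0.025 has power of about 0.67 instead of 0.77 at 13 per group, on the article's f = 0.5 and 2 degrees of freedom. Under a fixed order the first marker loses nothing, and the second depends on the first. The sample size was not derived from either marker, so these powers illustrate the relative cost only; they do not predict the trial's actual power.

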## Conclusions

In an attempt to better clarify the role of inflammatory mediators in the aging process, our group previously demonstrated the association among inflammatory mediators and functional outcomes and muscle strength in elderly community residents and inpatients [39,40]. Similarly, the literature provides evidence of IL-6 release after strenuous exercise in elderly persons and in youth. This release may bring a benefit by decreasing TNF-α levels [3,6-8,10,12,13]. However, the degree of intensity and the activity load, as well as the mechanism of this phenomenon, are not yet established. This trial was designed in order to be reproducible in a research environment and the clinical setting. We expect to collect results at the end of July 2010. We anticipate that the results will have implications in the development of new treatment strategies for elderly persons and the modification of their frail conditions.
